**Results:**

Data on the primary variable (depressive symptoms) and secondary variables (treatment-related distress, anxiety, fear of hypoglycemia, quality of life, treatment adherence, coping strategies and glycemic control) will be collected from the TG at the beginning/baseline, at the end of treatment and at 3, 6 and 12 months after treatment. The CG will be assessed at the beginning and at the end of the TG intervention. On completion of the program by the TG, the treatment will then be carried out in the CG.

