Clinical data and glycemic control will be collected through the medical record form of the visit to the physician and the data provided by the participant.

The primary variable is depression. Depressive symptoms during the previous 2 weeks will be assessed through a self-administered 7-item questionnaire (0–3), the BDI-FS [43]. For the diagnosis of depression, the Structured Clinical Interview for Major Depression Episode of the DSM-V will be used [44].

Among the secondary variables, fear of hypoglycemia will be evaluated with the Fear of Hypoglycemia questionnaire (FH-15) [45], which consists of 15 negative items on a Likert-type scale (1–5), and diabetes-related distress using the Spanish version [46] of the Diabetes Distress Questionnaire (DDS) by Polonsky et al., [47] which has 16 Likert-type items (1–5). The DDS provides a total distress score and 4 specific scores: affective distress; distress associated with the doctor-patient relationship; regimen-related distress and interpersonal distress. Quality of life will be assessed with the Diabetes Quality of Life Questionnaire [48], which evaluates quality of life specifically in individuals with diabetes mellitus. The Spanish version [49] has 43 questions (1–5) and 4 subscales: Dissatisfaction, Impact, Social/vocational concern and Concern for future aspects. Anxiety will be addressed using the Spanish version [50] of the State-Trait Anxiety Inventory (STAI) [51]. The STAI consists of 2 scales: State Anxiety (STAI-S) and Trait Anxiety (STAI-T). Each scale includes 20 self-administered items (0–3). Coping will be evaluated with the Spanish version [52] of the COPE inventory [53], composed of 5 scales assessing problem-centered coping, another 5 scales measuring emotion-centered coping, and 3 scales measuring less useful coping responses. Adherence to treatment will be evaluated with the 15-item (1–5) Spanish version of the Diabetes Self-Care Inventory-Revised questionnaire [54]. Personality will be evaluated using the Millon Clinical Multiaxial Inventory-III Spanish version [55]. This questionnaire contains 175 items with true or false answers. It consists of 11 basic personality scales, 3 pathological characteristics scales, 7 moderate syndrome scales and 3 severe syndrome scales.

The results of the trial will be published in peer-reviewed journals and presented in conferences.

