### Statistical analysis

First, a descriptive analysis will be conducted of the variables studied. For quantitative variables, measures of centralization and dispersion will be collected. For qualitative variables, a frequency analysis will be carried out.

To analyze cross-sectional and longitudinal differences, hypotheses will be contrasted at a 95% confidence level. To contrast differences between both groups (TG and CG) at baseline and post-treatment at a given time, Student’s *t*-test will be used (for strong violations of the normality assumption, the Mann-Whitney U-test) or analysis of variance (ANOVA). The effect size will be calculated using Cohen’s d.

To test whether the treatment produces differences over time (baseline, post-treatment, 3 months, 6 months and 12 months in the TG and baseline and post-treatment in the CG) in each of the groups, the *t*-test for related samples will be used (Wilcoxon signed-rank test in the event of strong violations of the normality assumption) or with an ANOVA for repeated variables and multiple regression model to control possible confounding variables (such as: age, gender, HbA1c, time with diabetes, etc.). For qualitative variables, McNemar’s test will be used.

To study the relationships between the different variables, Pearson’s correlation coefficient and linear regression models will be used for interval variables. The relationship between qualitative variables will be evaluated with the χ2 test.

Possible risk factors will be studied through logistic regression analysis (analysis of adherence to the treatment program).

The analyses will be carried out considering the subjects who complete the program. Analyses will also be carried out according to the protocol.

Analysis of the results will begin when the TG subjects have completed all of the phases of the treatment program. An improvement in the different variables will be taken into account in the following cases: significant differences in p≤0.05 and in the case of the BDI-FS when there is a decrease in the level of depressive symptomatology (moderate-mild, mild-minimum).

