### Sample size calculation

We calculated the effect size using Cohen’s [56] estimates for the calculation of sample size a priori. For this, the significance level was considered to be 0.05 and the power 0.80. Concerning the effect size, according to a recent review by Uchendu and Blake [14] on CBT in adults with diabetes, there is a moderate effect size (-0.43) in depression. Therefore, in our study, a moderate effect size (0.50) will be used. With these data, a sample size of 28 participants is needed. Since the study has 2 groups, 28 participants will be included in each of the groups (56 participants in total).

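### Improvement may be declared on any variable at p≤0.05, between or within arms, and the primary depression outcome is not fixed to one instrument and contrast

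*Protocol article*

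**What the plan says.** **Success rule (Statistical analysis, last paragraph).** "An improvement in the different variables will be taken into account in the following cases: significant differences in p≤0.05". The same sentence adds a separate condition for the BDI-FS, a fall of one severity level (moderate to mild, or mild to minimum). It does not say whether both conditions must hold or either is enough.

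**Tests to which the rule can apply (Statistical analysis).** "hypotheses will be contrasted at a 95% confidence level". TG and CG are compared by t-test, Mann-Whitney or ANOVA. Change within each arm is tested by paired t-test, Wilcoxon or repeated-measures ANOVA with regression. Within-arm testing covers four post-baseline times in the TG and one in the CG. Results are given for programme completers and also according to the protocol.

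**Primary variable.** The abstract has "Data on the primary variable (depressive symptoms" followed by seven secondary constructs. Results assessed has "The primary variable is depression", then assigns symptoms to the BDI-FS and continues: "For the diagnosis of depression, the Structured Clinical Interview for Major Depression Episode of the DSM-V will be used". Table 2 has two rows: depressive symptoms (BDI-FS) and depression (SCID).

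**Sample size calculation.** "the significance level was considered to be 0.05 and the power 0.80". The section refers to depression without naming an instrument.

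**The concern.** A trial's main claim should depend on one result that was fixed in advance. Here the text leaves open which instrument carries the claim, which contrast counts (TG versus CG, or change from baseline), and how the p-value and the severity-level drop combine. One threshold then applies to every variable, with no ranking.

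The within-arm route matters most. Under Procedure, participants enter with a BDI-FS score of at least 4 and below 13. Scores selected for being raised tend to fall on re-measurement, treated or not. A significant fall from baseline in the TG could therefore occur with an ineffective programme, and the rule as written would count it as improvement. The Conclusions section anticipates improvement both against the control group and against baseline, so this reading is not far-fetched.

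At stake are a depression claim that does not rest on the randomised comparison, and secondary improvements declared on isolated significant results.

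**Working it through.** **1. Does the text fix one primary test?**

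| Element | Where | What is stated |
|---|---|---|
| Primary, abstract | Abstract, Results | depressive symptoms; BDI-FS by Table 2 |
| Primary, methods | Results assessed | depression; SCID by Table 2, but both instruments follow in the text |
| Contrast | Statistical analysis | between groups and within groups; neither named primary |
| Time | Statistical analysis | post-treatment for TG versus CG; four post-baseline times within the TG |
| Success | Statistical analysis | p≤0.05, plus a BDI-FS level drop with an unclear link |

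No row settles the matter alone, and the first two differ. At least three routes to a depression claim remain: BDI-FS between groups, SCID between groups, and within-arm change on either.

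**2. How many outcomes does the rule reach?**

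- Secondary constructs in the abstract: distress, anxiety, fear of hypoglycemia, quality of life, adherence, coping and glycemic control = 7.
- With the BDI-FS and SCID: 7 + 2 = 9 instruments or measures.
- Scores described in Results assessed: BDI-FS 1 + SCID 1 + FH-15 1 + DDS 5 (total and 4) + DQOL 4 + STAI 2 + COPE 13 (5 + 5 + 3) + SCI-R 1 + HbA1c 1 = 29.

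**3. Chance of a false improvement.** The article gives no overall error rate to reproduce. Its 0.05 is a per-test level and sidedness is not stated; I take two-sided, the usual reading of a 95% confidence level. A false improvement must fall in the benefit direction, so its probability is 0.05 / 2 = 0.025 per test. With k independent tests and no effect, P(at least one) = 1 − 0.975^k and the expected number is 0.025k.

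| k | P(at least one), benefit direction | Expected number | P(any significance, either direction) = 1 − 0.95^k |
|---|---|---|---|
| 7 | 1 − 0.975^7 = 16.2% | 0.175 | 30.2% |
| 9 | 1 − 0.975^9 = 20.4% | 0.225 | 37.0% |
| 29 | 1 − 0.975^29 = 52.0% | 0.725 | 77.4% |

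**4. Effect of correlation.** The documents give no correlations, so common values of 0.3, 0.5 and 0.7 between test statistics are assumed. Benefit direction only:

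| k | 0.3 | 0.5 | 0.7 |
|---|---|---|---|
| 7 | 14% | 11% | 9% |
| 9 | 17% | 13% | 10% |
| 29 | 34% | 25% | 17% |

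**5. What these figures omit.** They count one test per outcome. The text allows up to six contrasts per outcome: one between groups, four within the TG and one within the CG. For 29 scores that is 6 × 29 = 174 tests. For the within-arm tests, chance error is also not the only problem, since regression to the mean can produce a real fall without any treatment effect.

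**The case against.** The strongest reply is that the primary instrument can be identified. The abstract's label matches the BDI-FS row of Table 2, the BDI-FS is the screening instrument, and it alone has its own criterion in the success rule. The SCID is assigned to diagnosis, and no section calls it a co-primary. This largely stands, and it makes the BDI-FS the natural choice. It does not settle the contrast, the time point or the link between p≤0.05 and the level drop, and Results assessed still uses the other label.

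The second reply is that unadjusted secondary tests do not inflate the error of a fixed primary test, and that adjustment is commonly left to an analysis plan. Both statements are right. The difficulty is that no primary test is fixed, and that the article states a rule for declaring improvement instead of leaving the matter open.

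A reader might infer more than the documents support:

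- **That an ineffective programme will probably show some improvement, with a chance of 77%.** That figure counts significance in either direction, assumes independence, and assumes that all 29 scores are tested. The article describes how the questionnaires are built; it does not say every subscale is tested. In the benefit direction the figure is 52% at most for one test per score, and 34% or less at the correlations tried.
- **That two co-primaries raise the primary error to 9.8%.** No co-primary is declared, and in the benefit direction two independent tests give 1 − 0.975^2 = 4.9%.
- **That a BDI-FS score alone admits participants, so many have no episode that could remit.** The inclusion criteria also require a psychological diagnosis of mild or moderate major depressive disorder, dysthymia or depressive symptomatology. The last of these admits some people without an episode, but the share is not given.

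**Conclusion.** The concern holds as a defect in the stated rule. The text permits a depression claim from either instrument and from within-arm or between-group testing, and it treats p≤0.05 on any variable as improvement. For one test per outcome, no true effect, independence and two-sided 0.05, the chance of at least one false improvement is about 16% (7 constructs), 20% (9 instruments) or 52% (29 scores, if all are tested). Correlation lowers these figures, and the within-arm and follow-up tests add to them by an amount the documents do not allow one to compute. The conclusion that one primary contrast must be fixed rests on the text and does not depend on these probabilities. The correction should be made before analysis begins.

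**What to change.** Reconcile the abstract, Table 2, Results assessed and Statistical analysis as follows.

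1. Name the BDI-FS total at post-treatment, TG versus CG, as the single primary test at 0.05.
2. Make SCID diagnosis a secondary outcome.
3. Present the BDI-FS severity-level drop as a supportive descriptive result, not as a criterion of success.
4. Replace the general p≤0.05 rule. Report secondary constructs, subscales, within-arm changes and follow-up visits as estimates with confidence intervals, labelled secondary or exploratory, without declaring efficacy.
5. Optionally, apply Holm adjustment over the 7 secondary constructs, with one prespecified score each, if formal secondary claims are wanted. Statisticians differ on whether this is needed, and it does not protect the primary test.

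The cost is wording only: no extra visits, data or participants. The downside is that secondary and within-arm claims become harder to make.

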### Sample size calculation

We calculated the effect size using Cohen’s [56] estimates for the calculation of sample size a priori. For this, the significance level was considered to be 0.05 and the power 0.80. Concerning the effect size, according to a recent review by Uchendu and Blake [14] on CBT in adults with diabetes, there is a moderate effect size (-0.43) in depression. Therefore, in our study, a moderate effect size (0.50) will be used. With these data, a sample size of 28 participants is needed. Since the study has 2 groups, 28 participants will be included in each of the groups (56 participants in total).

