#### Intervention

The web page will include the 9 sessions that comprise the CBT-based treatment (Table 1). The sessions will be weekly. Each week, the participant will find a brief summary of the previous session and an introduction to the topic being covered, with an explanation of the new session. The participant will then be provided with the new information (the subject matter) and various examples will be included to facilitate understanding. Once the information is introduced, a summary of the key ideas of the session will be presented and a short evaluation will assess the subject’s understanding. At the end of the session, the person will have the key ideas and a self-assessment of the session. Finally, the participant will receive an explanation of the task to be completed and forwarded to the therapist with an example of how the task should be carried out. The therapist will respond and provide feedback on the completed assignment, but no personal advice will be given. Each session will need to be completed in order to have the following session available. In addition, the participant will have a bibliography of each of the topics covered. Each session will last 20–30 minutes.

**Table 1 pone.0274551.t001:** Treatment sessions.

Session	Topic
1	What is depression? Relationship between cognitions, behavior and emotions. Relationship between diabetes and depression.
2	Relationship between stress and diabetes. Use of relaxation and physical exercise for the management of stress and diabetes.
3	Coping in diabetes. How to face the fears associated with diabetes (short-/medium- and long-term complications).
4	Identification, definition and resolution of problems. The demands of daily self-care.
5	Pleasurable activities. Incorporation of a physically and mentally healthy lifestyle plan.
6	Cognitive restructuring. Modification of beliefs and cognitive errors in diabetes.
7	Social skills: communication style. Working towards an assertive communication style. Communication with family, friends and medical professionals.
8	Importance of support. Searching for sources of support regarding diabetes.
9	Relapse prevention.

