We start from a treatment that is recognized as effective in the population in which it is to be applied [29–34] in depressive symptoms or depression and distress related to diabetes. However, no significant results were found regarding glycemic control, understood as the glycosylated hemoglobin (HbA1c) value. A possible explanation could be that, despite working with aspects related to the impact on the patient’s mood, changes in the treatment regimens for diabetes care are not directly addressed. This would make sense, as it is not the aim of this type of intervention. The study of other outcome variables of the web treatment on glycemic control, such as number of self-tests, episodes of hypoglycemia and hyperglycemia, and treatment adherence could add information along these lines. Moreover, other outcome variables with implications for treatment adherence, such as specific diabetes-related distress or fear of hypoglycemia, may also indicate structural changes that could influence long-term glycemic control. In addition, the number of sessions involved in treatment in previous studies has varied between 6 [32–36], 7 [37, 38] and 8 [29–31] treatment sessions. Based on previous studies and the existing relationships between depression and other variables in people with type 1 diabetes, in this study we have created 9 sessions.

Although it is known that adherence to Internet-based CBT treatment is lower than adherence when delivering the same treatment face to face [59], in the population with diabetes, there appears to be no difference between the two types of delivery [28]. Determining the variables involved in adherence to treatment will be among the data to be obtained in the present study. Accordingly, a comprehensive analysis of the medical and psychological variables involved in depression in people with diabetes, together with the variables that may affect adherence to this type of treatment in our study population, may help to provide greater insight into the effects of this treatment and the characteristics of the population in which it would be most beneficial (adherence), which are the main strengths of this study.

However, this study is not without limitations. The sample sizes of the previous studies are larger than the figure we aim to achieve in this study. Nevertheless, taking into account the rigor of the exclusion criteria and the sample size calculations described previously will enable reliable and valid conclusions to be drawn.

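### The stated power of 0.80 with 28 per group holds neither at the assumed effect of 0.50 nor at the cited effect of 0.43

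*Protocol article*

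**What the plan says.** The Sample size calculation section of the protocol article says it uses Cohen's estimates for an a priori calculation and gives the error rates: "the significance level was considered to be 0.05 and the power 0.80". Its one numerical piece of evidence is a review of CBT in adults with diabetes, and it goes from that figure to the planning value in two sentences: "there is a moderate effect size (-0.43) in depression. Therefore, in our study, a moderate effect size (0.50) will be used". From these inputs it derives 28 participants, and it enrols 28 in each of the two groups, 56 in all. It does not state the test, the sidedness or any dropout allowance behind the figure of 28.

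The Statistical analysis section compares treatment and control groups at a given time with Student's t-test (Mann-Whitney or ANOVA as alternatives). It also says "The effect size will be calculated using Cohen’s d" and "hypotheses will be contrasted at a 95% confidence level". It bases the analyses on participants who complete the programme.

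The Discussion concedes that earlier studies were larger. It then says that, together with the strictness of the exclusion criteria, "the sample size calculations described previously will enable reliable and valid conclusions to be drawn".

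**The concern.** Two things stand out. First, 0.43 becomes 0.50 through a *therefore* that rests only on both values being called moderate. No minimal important difference is given, and the earlier web-based trials are described as positive without effect sizes. The only quantitative evidence in the article is thus smaller than the effect used for sizing.

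Second, and more important, 28 per group looks far too few for a two-group comparison at either value. If so, the stated power is wrong as written, and the assurance in the Discussion rests on it. A trial reported as having 80% power invites readers to take a non-significant result as evidence that the programme does not work. If the real power is well below one half, such a result says little about an effect of the size the article cites.

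**Working it through.** **Inputs.** Significance level 0.05, power 0.80, effect sizes 0.50 (used) and 0.43 (cited, absolute value), and 28 per group with equal allocation, all from the Sample size calculation section. The independent-groups t-test and Cohen's d come from the Statistical analysis section. Assumptions: both effects are standardised mean differences between groups (SD = 1), and there is no dropout. Sidedness is not stated, so both cases are shown.

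**Step 1: try to reproduce 28 per group at d = 0.50.** Normal approximation: n per group = 2(z_α + z_0.80)² / d².
- Two-sided: 2(1.960 + 0.842)² / 0.50² = 15.70 / 0.25 = 62.8, so 63. The noncentral t gives 64.
- One-sided: 2(1.645 + 0.842)² / 0.50² = 12.37 / 0.25 = 49.5, so 50. The noncentral t gives 51.

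The figure of 28 is not reproduced. Nearby numbers come only from other calculations. A one-sided paired or one-sample t-test at 0.50 needs 27 participants (34 two-sided), and a two-sided test of a correlation of 0.50 needs about 29. Neither is the between-group comparison. An ANCOVA needs n = 2(1.960 + 0.842)²(1 − ρ²) / d². Setting n = 28 and d = 0.50 gives 1 − ρ² = 28 × 0.25 / 15.70 = 0.446, so ρ is about 0.74, a baseline correlation that the article does not assume.

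**Step 2: the same calculation at the cited 0.43.**
- Two-sided: 15.70 / 0.1849 = 84.9, so 85. The noncentral t gives 86.
- One-sided: 12.37 / 0.1849 = 66.9, so 67. The noncentral t gives 68.

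The required size is (0.50 / 0.43)² = 1.35 times that for 0.50.

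**Step 3: power of the planned 28 per group.** Normal approximation: power = Φ(d√(n/2) − z_α), with √(28/2) = 3.742.
- d = 0.50, two-sided: Φ(1.871 − 1.960) = Φ(−0.089) = 0.46
- d = 0.43, two-sided: Φ(1.609 − 1.960) = Φ(−0.351) = 0.36
- d = 0.50, one-sided: Φ(1.871 − 1.645) = Φ(0.226) = 0.59
- d = 0.43, one-sided: Φ(1.609 − 1.645) = Φ(−0.036) = 0.49

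The exact noncentral t values are slightly lower:

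| Test | Power at 0.50 | Power at 0.43 | Stated power |
|---|---|---|---|
| Two-sided | 0.45 | 0.35 | 0.80 |
| One-sided | 0.58 | 0.48 | 0.80 |

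**Step 4: smallest effect detectable with 80% power at 28 per group.** Normal approximation: d = (z_α + z_0.80) / 3.742. This is 2.802 / 3.742 = 0.75 two-sided and 2.487 / 3.742 = 0.66 one-sided. The noncentral t gives 0.76 and 0.67.

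**The case against.** The strongest reply concerns the choice of 0.50. The section says at the outset that it works with Cohen's estimates, so a natural reading is that the review selects the category and a conventional value for that category is used. That is a disclosed choice on which statisticians may differ. No interval is given for the review's estimate, so 0.50 cannot be shown to conflict with it. The comparators behind the review's figure are not described either, so 0.43 cannot be shown to be the right expectation for this trial. This objection stands.

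A reader might go further and infer that nothing in the article could support an effect above 0.43, pointing to web delivery and limited therapist input ("The therapist will respond and provide feedback on the completed assignment, but no personal advice will be given"). The article does not support that. It describes a waiting-list control, content built for type 1 diabetes, nine sessions against six to eight in earlier web programmes, and e-mail and telephone prompts. The authors do not tie these features to 0.50 and no size is attached to them, but they are possible grounds. Nor does the article show that the limit on personal advice lowers the effect.

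A reader might also infer that 0.80 power is reached at 0.50 and lost only by rounding up from 0.43. Step 3 shows otherwise: two-sided, about 35 points are already missing at 0.50, and moving to 0.43 removes about 10 more.

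Finally, no section plans to interpret a null result as evidence of no effect, and the Discussion admits the smaller sample. The risk of misreading is therefore an inference, though the reassurance that follows that admission invites it. None of these points rescues the stated power.

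**Conclusion.** The point holds in a limited form. The effect size of 0.50 is poorly justified but is not an error in itself. The error is the statement that 28 per group gives power 0.80: for the planned between-group t-test the power is about 45% at 0.50 and 35% at 0.43 two-sided, or 58% and 48% one-sided. The shortfall against 0.80 runs from 22 to 45 percentage points across these cases. At the cited effect, the trial would miss a true benefit about 65% of the time two-sided and 52% one-sided.

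This rests on the assumptions listed in the working: independent groups, both effects on the standardised mean difference scale, no dropout, and no gain from baseline adjustment. Strong baseline adjustment would raise power, but the article does not build it into the calculation. Dropout would lower power, because the analysis uses completers.

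**What to change.** Enrolment stays at 28 per group; only wording changes.

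- **Sample size calculation.** Replace the 0.80 power statement with the power of 28 per group at both 0.50 and the cited 0.43, and add the smallest effect detectable with 80% power. State the test and its sidedness. Either give a reason for 0.50 or present it only as a convention. Replacing 0.50 with 0.43 while leaving 28 and 0.80 in place would not repair the section, because the mismatch would grow.
- **Discussion.** Replace the assurance about reliable and valid conclusions with a statement that an effect of the cited size may well be missed, and that a null result would not rule it out.

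The cost is a less favourable stated power and a more cautious claim about what the trial can show.

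### 28 per group does not give 80% power at d = 0.50: the planned two-group comparison has about 45% power and would need 64 per group

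*Protocol article*

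**What the plan says.** The protocol article, Sample size calculation, gives three inputs. On error rates: "the significance level was considered to be 0.05 and the power 0.80". On the external evidence, from a review of CBT in adults with diabetes: "there is a moderate effect size (-0.43) in depression". On the planning value: "in our study, a moderate effect size (0.50) will be used". It concludes "With these data, a sample size of 28 participants is needed" and, because there are two groups, assigns 28 to each, 56 in total. The section names neither the test nor its sidedness, and makes no allowance for loss.

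Statistical analysis plans Student's t-test (Mann-Whitney or ANOVA as alternatives) for treatment versus control at post-treatment, with Cohen's d as the effect measure, and states that "hypotheses will be contrasted at a 95% confidence level". Paired tests, repeated-measures ANOVA and multiple regression are listed for change over time in each group. The analyses use participants who complete the program.

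The Discussion concedes that earlier studies were larger, but then states that the rigor of the exclusion criteria and "the sample size calculations described previously will enable reliable and valid conclusions to be drawn".

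**The concern.** The trial randomises to treatment or waiting list, and the Conclusions section anticipates improvement relative to the control group. That comparison is the one the sample size has to support. For two independent groups, 28 per group is well known to be too few for a half-SD difference, so the stated 80% power looked wrong by a wide margin.

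If it is wrong, the trial is more likely to miss its own planned effect than to detect it. A non-significant result could not rule that effect out, and a significant one would tend to overstate the effect. The Discussion's reassurance to readers rests on the same calculation.

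**Working it through.** **Inputs.** Alpha 0.05, power 0.80, d = 0.50, 28 per group and the review's 0.43 are from Sample size calculation. The two-group t-test is from Statistical analysis. Two-sided testing is inferred from the 95% confidence level; one-sided is also shown.

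**1. Trying to reproduce 28 per group.** The normal approximation for two independent means is n per group = 2(z₁₋α/₂ + z₁₋β)² / d².

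- Two-sided, d = 0.50: 2 × (1.960 + 0.842)² / 0.25 = 62.8, so 63. The exact noncentral-t solution is 63.8, so **64 per group, 128 in total**.
- One-sided, d = 0.50: 2 × (1.645 + 0.842)² / 0.25 = 49.5, so 50. Exact: 50.2, so 51 per group.
- Two-sided, d = 0.43: 2 × (1.960 + 0.842)² / 0.1849 = 84.9, so 85. Exact: 85.9, so 86 per group.

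No two-group t-test gives 28.

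**2. Power with 28 per group.** The noncentrality parameter is d√(n/2), with 54 degrees of freedom and a two-sided critical value of 2.005.

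| Effect | Noncentrality | Two-sided power | One-sided power |
|---|---|---|---|
| 0.50 | 0.50 × √14 = 1.87 | 0.451 | 0.580 |
| 0.43 | 0.43 × √14 = 1.61 | 0.352 | 0.478 |

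Solving for the effect detectable with 80% power at 28 per group gives d = 0.76 two-sided and 0.67 one-sided.

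**3. Calculations that do land near 28.** None of these sizes the randomised comparison at d = 0.50.

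- Paired t-test in a single group, d = 0.50: 33.4, so 34 two-sided; 26.1, so 27 one-sided. With the Wilcoxon efficiency factor 3/π, the one-sided figure is 27.4, so 28. The control group plays no part.
- Repeated-measures ANOVA, group-by-time interaction, f = 0.25, correlation 0.5: 34 at two time points and 28 at three. This is the total N, not the number per group, and the control group has only two assessments before it starts treatment.
- A test of a correlation of 0.5: 29 in total. This is a different effect measure.

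The article does not say which calculation was used, so the origin of 28 cannot be settled.

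**4. Baseline adjustment.** The article gives no baseline-outcome correlation, so r is assumed. Adjustment raises the effective effect to d/√(1 − r²).

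| Assumed r | Power at 28 per group, d = 0.50 | n per group for 80% |
|---|---|---|
| 0.3 | 0.49 | 59 |
| 0.5 | 0.56 | 49 |
| 0.7 | 0.73 | 34 |
| 0.75 | 0.79 | 29 |

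Power passes 0.80 at r of about 0.76. At d = 0.43, even r = 0.75 gives only 0.67.

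**5. Loss.** The analysis is on completers, and no loss rate is given, so the completer numbers are assumed. The noncentrality is d√(n₁n₂/(n₁ + n₂)), here with d = 0.50.

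- 24 treated, 28 control: 0.50 × √12.92 = 1.80, 50 df, power 0.42.
- 20 treated, 28 control: 0.50 × √11.67 = 1.71, 46 df, power 0.39 (0.30 at d = 0.43).
- 20 in each group: 0.50 × √10 = 1.58, 38 df, power 0.34.

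**The case against.** The section on sample size names neither test nor sidedness, and the analysis section offers several methods without fixing one. The 45% is therefore the two-sided, unadjusted t-test case. This is correct and the figure should carry that label, but one-sided testing gives 58%, and baseline adjustment reaches 80% only at a correlation that the article neither states nor supports.

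The move from 0.43 to 0.50 is disclosed. It is an optimistic judgement and not an arithmetic error, and without the cited review its relevance to a waiting-list contrast cannot be judged. That stands: the 0.43 figures are sensitivity results, and the main discrepancy arises at the article's own 0.50.

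The number of completers is assumed, and a loss allowance might appear in a fuller protocol. That also stands; loss only worsens a shortfall that exists with every participant retained.

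A null result would not be wholly uninformative. With 28 per group the 95% interval has a half-width of about 2.005 × √(2/28) = 0.54 SD, so an estimate near zero would exclude large effects. It would not exclude the planned 0.50, and that is the relevant weakness.

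Finally, the Discussion does list the smaller sample as a limitation. It then cancels that warning by appealing to the calculation.

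**Conclusion.** The concern holds. With the article's own alpha, power and effect size, the randomised comparison needs 64 per group, and the planned 28 is less than half of that. Power is about 45% at d = 0.50 and 35% at 0.43, and the effect detectable with 80% power is about 0.76 SD. These figures assume a two-sided, unadjusted, equal-allocation t-test with no loss. The conclusion survives one-sided testing and any baseline correlation below about 0.76, and it does not depend on how 28 arose. Because all the inputs and the result are printed, this is an error of statement and not a detail left to another document.

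**What to change.** In Sample size calculation, name the test and its sidedness, and replace the 80% claim with what the design delivers: for a two-sided two-group t-test, 28 per group gives about 45% power at d = 0.50 and 35% at 0.43, and 80% power only for d of about 0.76. If a baseline-adjusted comparison becomes the primary analysis, quote its power instead, with the assumed correlation stated: 0.49 to 0.56 at d = 0.50 for correlations of 0.3 to 0.5. Note that loss to the completer analysis lowers these figures.

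In the Discussion, remove the assurance that the calculation secures reliable and valid conclusions, and state the limited power as a limitation. Make the between-group estimate with its confidence interval the main result.

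The cost is rewording and a less favourable power statement; no extra participants are needed. If the sponsor prefers to keep 80% power at d = 0.50 with the unadjusted test, the price is 128 participants in place of 56, that is 72 more.
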